### Setting/population

Better Start Bradford provides services to families in three areas of Bradford, the population of which make up approximately 12% of the entire Bradford area. These three inner-city areas are ethnically diverse and are among the most deprived both in Bradford and in England [11]. In terms of language and communication needs, recent government statistics show that 20% of children in the Bradford area do not achieve expected levels of development in communication and language compared to a national average of 18% [13]. In the Better Start Bradford areas, recent estimates suggest that these figures are higher, with approximately 23.5% of children not achieving expected levels in language and communication [14].

### Intervention

The Talking Together programme takes a two-step approach. Firstly, a universal language screening (see the “Screening measures” section below) is provided to the community by BHT Education and Training, in which the programme is successful in seeing over 65% of the eligible population. From this screening data, language development workers (LDWs; early year’s practitioners with specific training in children’s early language development) are able to identify families who may benefit from the programme based on both child factors (i.e. weak language development) and parent or home characteristics (e.g. parent-child interaction, a lack of developmentally appropriate materials in the home). This combined approach to identifying appropriate recipients of intervention is in line with the recent recommendations provided by the Education Endowment Foundation and Public Health England [6]. The intervention aspect of Talking Together draws on research emphasising the role of positive parent-child interaction in early language development and equips parents with the skills and knowledge to provide a supportive home learning environment. Talking Together currently serves a culturally diverse and deprived inner-city population, and the programme was developed to be appropriate for delivery to families from a range of cultural and linguistic backgrounds. This is a particular strength of the programme, given the growing need for interventions that can adapt to the needs of the increasingly diverse UK population.

Talking Together is delivered by trained LDWs in the child’s home on a 1:1 basis with individual parents/carers. The programme consists of six weekly, hour-long sessions followed by a review approximately 3 to 4 months after the intervention. The Talking Together programme aims to give parents/carers the knowledge, understanding, and tools to improve their child’s communication skills. Weekly sessions cover five topic areas related to improved language and communication, including what is communication, play, attention and listening, turn taking, praise and encouragement, and a final overview session. During these sessions, LDWs provide information about the week’s core topic and then engage parents in conversation about their understanding of the topic and how they address it in their home. For example, on the topic of play, the session would present factual information on the importance of play for learning, and LDWs would then discuss parents’ own experiences of play as a child and now with their own child. In addition to this, LDWs observe parents’ interactions with their child, and then use a range of techniques to highlight parents’ positive behaviours and support identification and change of less beneficial behaviours. These techniques include praising, modelling of good practice, and providing suggestions and examples for parents to try themselves. A central premise of Talking Together is that it takes a positive, child-centred approach that focuses on improving the child’s learning environment, rather than a parent-centred approach that focuses on caregiver responsibility and aptitude. This helps to ensure that conversations are constructive, and parents feel supported rather than judged in their parenting.

Practitioners are required to follow a programme manual, which contains session content for each week, activities for parents to complete between sessions, and information resources for parents. Although Talking Together is manualised and there is an expectation of fidelity to the programme, it is also personalised to be as suitable as possible to individual families. LDWs are encouraged to use their extensive training to ensure that content is engaging, relevant, and useful as possible for participants. They do this by getting to know the family’s needs and interests, and using this understanding to provide bespoke examples and activities around the core content. In addition to this, the sixth and final review session is an opportunity for the family and LDWs together to decide what content from the programme they would like to consider in more depth. The LDWs then tailor this session to be most useful for each individual family.

LDWs also take books and simple play resources/toys to sessions to give parents ideas on how to play with their child and develop communication skills. As well as delivering the session content in the home, LDWs also assess whether the home provides a good learning environment, looking for distractions that may be disruptive to learning/communication development, and advising families on how to improve the home learning environment.

#### Training and quality assurance

The service provider has robust procedures to train and support new members of staff, and monitor implementation across all staff members, to ensure fidelity. New staff members are trained over a period of several months, including participating in a range of mandatory courses and extensive shadowing of other LDWs’ practice. All staff deliver at least one full course of the intervention in conjunction with another LDW before being approved for independent practice.

With regard to quality assurance, all sessions are delivered with strict adherence to the manual and delivery guidelines, and this is monitored through regular observations of practice. All staff members receive at least two observations and evaluations of their session delivery every year by a senior LDW. Session observations are video recorded, and staff review their delivery with a senior member of staff to ensure that programme content is fully covered and practitioners’ skills are supported and developed. In addition to this, all staff participate in regular supervision with members of the senior staff, to further ensure consistency in programme delivery and staff members’ professional practice.

#### Comparator

At present, Talking Together operates a waiting list and a proportion of families therefore naturally experience a delay between referral and intervention. The maximum waiting time any family should experience under standard practice is 6 months. For the study, families allocated to the waiting control group will receive Talking Together 6 months after their baseline assessment; mirroring and not exceeding the current maximum wait time for families. At this point, they will be reassessed before they receive the Talking Together intervention as part of routine care. If at this reassessment the LDW concludes on the basis of the assessment measures that the family no longer requires Talking Together, they will be discharged from the service as is standard practice.

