### Design

This will be a two-arm randomised controlled feasibility study, with an experimental group and a waiting control group. Families will be randomised following baseline data collection collected at the standard universal screening assessment delivered in the home. The families allocated to the experimental group will receive the Talking Together programme within approximately 2 weeks of allocation, while the families allocated to the waiting control group will receive the programme after a 6-month waiting period. While the average waiting time in standard practice varies depending on a number of factors, with the majority of families seen within 3 to 4 months, many families wait up to 6 months for intervention. In order that we can ensure time of data collection is comparable across the intervention and waiting control groups, we have time-locked the assessments at 2 and 6 months following pre-test thereby mirroring but not exceeding the maximum wait time. Families will be fully informed of the timeline of the project at recruitment, it will be made clear that families do not have to participate in oTTer to receive Talking Together, and full information regarding withdrawal procedures will be provided.

Feasibility and implementation outcomes will be measured using child language assessments, measures of home learning environment and parent-child relationship, and monitoring data in the form of, for example, referral rates, waiting times, attrition rates, and completion rates.

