#### Screening measures

The Universal Language Assessment (baseline) is comprised of two measures, which are used in conjunction with observation of the home and parent-child interaction to inform LDWs’ judgement about referral to the intervention:
BHT Language Screener Measure: this assessment was created by BHT in conjunction with speech and language therapists as well as academic partners. It is comprised of ten statements about children’s current language skills scored on a 3-point scale (the child does not do this yet, does this sometimes, does this often). LDWs also record their specific reason for referring into the programme (language and communication, child behaviour, parent behaviour, home learning environment, supporting a family with complex needs).The Oxford Communication Development Inventory-Short (CDI-Short) [22]: a validated measure of early language development comprised of 100 vocabulary items. Parents complete this with the support of the LDW and indicate words the child can (a) say and (b) understand. This measure is used as an indication of conceptual vocabulary, and parents are asked to indicate which words their child can say and understand in any of the languages they speak. It is a parent-report measure that takes approximately 10 min to complete

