### Data collection

As our outcome measures are administered routinely by LDWs, and in order to avoid repeat assessments, data will be collected by both LDWs and research staff. Baseline data will be collected during universal language assessment sessions by LDWs as standard practice. Pre-test and post-test data will be collected by LDWs for the experimental group and RAs for the waiting control group. Six-month follow-up assessments in both treatment arms will be carried out by trained RAs accompanied by a LDW familiar with the family to maintain consistency and make clinical judgements about the need for ongoing input. LDWs and RAs will receive the same training in administering the assessments and will carry out reciprocal observations of assessments. The timeline for assessment can be seen in Fig. 3.

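### The control group's 6-month point is timed from two different origins, so a wait within the 6-month maximum is not assured

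*Protocol article*

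**What the plan says.** **The cap.** Comparator: "The maximum waiting time any family should experience under standard practice is 6 months". The section describes the wait as running from referral to intervention.

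**Origin 1, baseline.** Comparator says the "waiting control group will receive Talking Together 6 months after their baseline assessment", "mirroring and not exceeding the current maximum wait time for families". It adds: "At this point, they will be reassessed before they receive the Talking Together intervention as part of routine care". Research questions (Aim 1) also places follow-up 6 months after baseline. Data collection places the end of follow-up at approximately that time.

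**What baseline is.** Screening measures: "The Universal Language Assessment (baseline) is comprised of two measures". Data collection: "Baseline data will be collected during universal language assessment sessions by LDWs as standard practice". Design also places baseline collection at the screening assessment, with randomisation after it.

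**Origin 2, pre-test.** Design: "we have time-locked the assessments at 2 and 6 months following pre-test thereby mirroring but not exceeding the maximum wait time". Progression criteria counts a pre-test as on time if it is no more than 1 month after the screener, and a follow-up as on time if it is 5.5 to 6.5 months after pre-test.

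**What families are told.** Design: "Families will be fully informed of the timeline of the project at recruitment".

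**The concern.** One visit has two time origins, and the second is later than the first. The claim to stay within the maximum wait is attached to both, but a schedule that runs 6 months from a later origin does not stay within 6 months of the earlier one.

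Two things are at stake. First, the cap is how the protocol defends the waiting control. Design says that most families are ordinarily seen within 3 to 4 months, so the assurance that nobody waits longer than routine practice allows carries weight. A timeline for families built on the Comparator wording would understate the wait.

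Second, timing adherence is one of the three progression criteria. If pre-test is more than 0.5 month after screening, staff who hold strictly to 6 months from baseline would see controls before the 5.5-month limit, and those visits would be scored as non-adherent. Staff who are scored as adherent would pass 6 months from screening.

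**Working it through.** **Inputs**
- Gap from screening to pre-test, t: 0 to 1 month (Progression criteria).
- Follow-up after pre-test: nominal 6 months (Design), adherent from 5.5 to 6.5 months (Progression criteria).
- Cap: 6 months (Comparator).

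**The plan's own figure.** The stated 6 months from baseline is reproduced at the nominal visit only when t = 0, that is, with pre-test on the day of screening.

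**Is t = 0 realistic?** Pre-test is done by language development workers in one arm and research assistants in the other (Data collection), so it must come after allocation. Allocation is run once a week on referrals already entered (Recruitment and randomisation). A positive gap is therefore built in.

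**Planned gap.** The intervention arm starts about 2 weeks after allocation (Design). Its pre-test has to come before that, and control assessments are to align with it. Assuming that referrals are entered promptly, t is at most about 1 + 2 = 3 weeks, or 21/30.4 ≈ 0.7 month.

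**Formulas, in months**
- Nominal follow-up after screening = 6 + t
- Adherent window after screening = 5.5 + t to 6.5 + t
- Share of the window's length later than 6 months = min(1, 0.5 + t)
- Six months from screening, counted from pre-test = 6 − t

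| t | Nominal follow-up | Adherent window | Share of window after 6 months | 6 − t |
|---|---|---|---|---|
| 0 | 6.0 | 5.5–6.5 | 50% | 6.0 |
| 0.25 | 6.25 | 5.75–6.75 | 75% | 5.75 |
| 0.5 | 6.5 | 6.0–7.0 | 100% | 5.5 |
| 0.7 (planned) | 6.7 | 6.2–7.2 | 100% | 5.3 |
| 0.75 | 6.75 | 6.25–7.25 | 100% | 5.25 |
| 1.0 | 7.0 | 6.5–7.5 | 100% | 5.0 |

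The share describes the length of the window and is not a forecast of families. When t exceeds 0.5, the value 6 − t drops below 5.5, so a strict 6-months-from-baseline visit and the adherence window cannot both be met.

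**Other clocks**
- Wait counted from entry of the referral, r months after screening: the nominal wait is 6 + t − r. Entry precedes allocation and allocation precedes pre-test, so r < t. The overrun shrinks but stays positive.
- Baseline read as pre-test (t = 0): the window still ends at 6.5 months, 0.5 month past the cap.

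All figures bound the follow-up visit. If that visit is the reassessment, the programme starts later still.

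**The case against.** Several objections have force.

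- **The clock.** The wait is defined from referral, and no separate referral date is given. Sample size describes a family about to be referred at the end of the screening visit, and the referral is entered on the record system afterwards. Counting from that entry reduces the overrun. It does not remove it, because entry still comes before pre-test.
- **The gap.** The 1-month limit is a tolerance. The planned sequence suggests about 0.7 month at most, so about 6.7 months describes the plan better than 7.0.
- **The window.** The 5.5 to 6.5 month band is for scoring visits. It does not show an intention to keep families waiting to its end, and the 7.5-month figure needs the latest allowed pre-test and the latest allowed follow-up together.
- **The link between visits.** No section says outright that the Comparator reassessment is the 6-month follow-up. The reading rests on both being set at 6 months, and on a language development worker attending follow-up to judge the need for further input (Data collection), which matches the discharge decision in Comparator. Fig. 3, on assessment timing, is not available here.
- **Strictness.** Data collection says approximately 6 months. The direct clash with the adherence window therefore holds only if the Comparator's 6 months is read strictly.

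A reader might infer more than the text supports:

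- *Every control family breaches the cap.* Not so: a pre-test within 0.5 month of screening and an early follow-up can keep it.
- *The comparison is biased.* Not so: both arms are timed from pre-test.
- *Families have been misinformed.* This cannot be said, because the information sheet is not shown.
- *7.5 months is the longest wait.* It is not: green for adherence requires 80%, so up to 20% may fall outside the window.

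**Conclusion.** The point holds as an inconsistency in timing. With baseline as the screening visit and the 6-month visit timed from a later pre-test, the statement that the 6-month maximum is not exceeded is not assured. Counted from screening, the nominal overrun is above 0 and up to 1 month, or about 0.7 month on the planned sequence. It reaches 1.5 months only at both adherence limits.

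This rests on two assumptions: that the reassessment before the controls' programme is the 6-month follow-up, and that the wait runs from about the screening visit. A later clock start makes the overrun smaller. No estimate or between-arm comparison is affected. What changes is the accuracy of the stated wait and which visits count as adherent. Severity is minor to moderate.

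**What to change.** 1. Use pre-test as the single origin for the 6-month point in Research questions, Comparator, Design, Data collection and Progression criteria.
2. State that controls are reassessed at a target of 6 months after pre-test (adherence window 5.5 to 6.5 months) and start the programme promptly afterwards.
3. Replace both claims of staying within the maximum wait with wording such as: *The reassessment is usually between 6 and 7 months after screening, and up to 7.5 months for a visit within the adherence window.* Do not call 7.5 months a maximum.
4. Make sure that the timeline given to families says this. The trial is already recruiting (Trial status), so control families already enrolled should be told if what they were given differs.

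This needs no extra visits, families or analyses and leaves the time-locking of the two arms intact. The cost is a somewhat longer stated wait and a revised family timeline.

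If the service's 6-month cap is binding, the sponsor should instead schedule the controls' follow-up, and the matching visit in the intervention arm, to end by 6 months after screening, and move the adherence window to match. That costs follow-up time: with pre-test 1 month after screening, the visit could be no later than 6 − 1 = 5 months after pre-test.

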### Design

This will be a two-arm randomised controlled feasibility study, with an experimental group and a waiting control group. Families will be randomised following baseline data collection collected at the standard universal screening assessment delivered in the home. The families allocated to the experimental group will receive the Talking Together programme within approximately 2 weeks of allocation, while the families allocated to the waiting control group will receive the programme after a 6-month waiting period. While the average waiting time in standard practice varies depending on a number of factors, with the majority of families seen within 3 to 4 months, many families wait up to 6 months for intervention. In order that we can ensure time of data collection is comparable across the intervention and waiting control groups, we have time-locked the assessments at 2 and 6 months following pre-test thereby mirroring but not exceeding the maximum wait time. Families will be fully informed of the timeline of the project at recruitment, it will be made clear that families do not have to participate in oTTer to receive Talking Together, and full information regarding withdrawal procedures will be provided.

Feasibility and implementation outcomes will be measured using child language assessments, measures of home learning environment and parent-child relationship, and monitoring data in the form of, for example, referral rates, waiting times, attrition rates, and completion rates.

Based on the recent MRC guidance [15], our qualitative evaluation is underpinned by the conceptual framework for implementation fidelity by Hasson [16], e.g. focusing on measures of adherence and potential moderators. This framework is embedded within our wider implementation evaluation work [17]. Qualitative data will be collected through interviews with service providers to explore any issues with running the programme as part of a trial. These interviews will take place immediately after follow-up assessment has been completed for the intervention group. In addition, we will invite a sample of oTTer families to take part in structured interviews to explore their experiences of participation in the oTTer project. Topic guides will be based on the Theoretical Domains Framework, a widely used framework in behaviour change and implementation research [18, 19]. While the conceptual framework for implementation fidelity is the overall evaluation framework and outlines the key research questions, use of the TDF allows an in-depth exploration of the barriers and facilitators of implementing the trial.

While this research is being carried out within a diverse community, interpreters will not be used in the delivery of the Talking Together programme or any of the data collection. The eligibility criteria state that families must speak one of either English, Urdu, or Punjabi to their child and we have LDWs, RAs, and PDRAs who can speak to the families in their home language without the use of interpreters.

### Eligibility

#### Families

##### Inclusion

The inclusion criteria for families are as follows:
Families must live in the Better Start Bradford reach area.Families must have a child aged two to two and a half years when referred into the Talking Together programme following a screening assessment by a LDW.Families must be willing to receive the intervention delivered by a LDW in their home.Families need to allow the intervention programme to be delivered with the same primary parent/carer at each session. More than one parent/carer may be present at the sessions, but there must be one consistent parent/carer who is present at all sessions.Families must be willing to be randomly allocated to treatment or control group and consent to additional data collection if allocated to the control group.Families must speak English, Urdu, or Punjabi as the primary language with their child established via assessment and observation by a language development worker.

